### 2.5 Treatment

DATE-TCM does not restrict the application of western medical treatment methods, and related information will be systematically recorded. Patients are commonly treated with high dose of intravenous steroid during the relapse phase, which usually refers to intravenous administration of 1 g or 500mg of glucocorticoid per day for 3-5 consecutive days, halved every 3 days. Plasma exchange and immunoabsorption therapies are also optional treatment in the relapse phase. Immunomodulatory therapies including low dose steroid, immunosuppressants (Azathioprine, Mycophenolate, etc.), and DMTs (fingolimod, Teriflunomide, Rituximab, satralizumab, etc.) are necessary for the remission phase. In addition, DATE-TCM will particularly detailed document the application of TCM, such as the timing of TCM application (relapse or remission phase), the types of TCM (defined according to the World Health Organization including the CHM, acupuncture, moxibustion, massage, taiji, qigong, etc.), and CHM relevant information (dose, frequency, duration, and adherence to TCM treatment of herbs, herbal materials, herbal preparations, or finished herbal products) in the entry and follow-up visits (Song et al., 2022).

### 2.6 Outcome measurements

The primary and secondary outcomes are listed in Table 2. The primary outcome is the Annualized Aggregate Relapse Rate, defined as the number of confirmed relapses within a year. A relapse is defined as the appearance of a new or worsening previously stable or improving pre-existing neurological abnormality, separated by at least 30 days from onset of a preceding relapse. Such abnormalities must be present for at least 24 h and occur in the absence of fever or infection.

**TABLE 2 T2:** The outcomes of DATE-TCM study.

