## Abstract

**Background:** Traditional Chinese medicine (TCM), a main form of complementary and alternative medicine provides a potential possibility for demyelinating disease of the central nervous system (DDC) management and has been applied in considerable amounts of patients with this disorder. Nevertheless, powerful real-world evidences regarding the epidemiological and clinical characteristics, safety, and outcomes of TCM in DDC are lacking. The primary objective of the Demyelinating Diseases of the Central Nervous System Registry for Patients with Traditional Chinese Medicine (DATE-TCM) is to create an organized multicenter data collection structure to define integrative characteristics of DDC patients treated with TCM in an endeavor to fill these knowledge gaps to better inform clinical care and health policy.

**Method:** This study provides a prospective and voluntary registry by using a web-based system. Baseline data will be recorded and subsequently regular follow-up visits will be implemented every 3–6 months for a total of 5 years. The primary outcome is Annualized Aggregate Relapse Rate at 5-year follow-up.

**Results:** DATE-TCM is currently designed to capture the multidimensional (epidemiologic, demographic, clinical, etc.) features of DDC patients receiving TCM treatment, the type and long-term safety and efficacy of TCM intervenes in the DDC populations, as well as the interaction of TCM treatments and disease modifying therapies in the management of DDC, aiming to include 2000 eligible adult DDC patients with TCM intervenes from 35 participating centers, covering 77.4% of provincial administrative regions of mainland China.

**Conclusion:** DATE-TCM is the first, largest, most geographically extensive, and standard registry-based observational study that systematically document the real-world data regarding the TCM application in the DDC populations, which will be extraordinarily important for clarifying the comprehensive characteristics and outcomes of TCM in DDC, further shed light on standardizing and optimizing the TCM measures for DDC management and establishing evidence-based clinical practice guidelines for TCM application in DDC.

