The follow-up plan was developed with reference to the relevant elements of DDC registry studies from other regions or countries and the characteristics of TCM treatment. Demographics, symptoms, and comorbidities variables, treatment status, safety assessments, Cerebro-Spinal Fluid (CSF) or other examinations (e.g., evoked potentials) results, Body mass index (BMI), EDSS, four examinations of TCM, and relapse information will be follow-up every 3 months by telephone or face-to-face visits. The Multiple Sclerosis Functional Composite (MSFC), Symbol Digit Modalities Test (SDMT), fatigue severity scale (FSS), Multiple Sclerosis impact scale (MSIS), and EuroQol-5D (EQ-5D) assessments will be administrated every 6 months through face-to-face visits. Blood leukocyte count and classification count, blood liver and renal functions test, serum neurofilament light chain (NFL), serum cytokines, serum anti-AQP4 IgG, and serum anti-MOG IgG will be tested every 6 months. MRI related evaluation of brain and spinal cord will be conducted every 12 months.

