**Primary outcomes**
Annualized Aggregate Relapse Rate

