**Secondary outcomes**
Total number of adverse events during evaluation
Percentage of participants with adverse events
Time to 3-month sustained disability progression
Time to 6-month sustained disability progression
Number of new or newly enlarging T2 hyperintense lesions as measured by magnetic resonance imaging (MRI)
Number of gadolinium-enhancing T1-weighted lesions as measured by MRI
Percent change in brain volume as measured by MRI
Change in multiple sclerosis functional composite (MSFC) score
Change in symbol digit modalities Test (SDMT) score
Chance in fatigue severity scale (FSS) score
Change in euroQol- 5 dimension (EQ-5D) score
Change in multiple sclerosis impact scale (MSIS) score

The Secondary outcomes include total number of adverse events (AE, any unfavorable and unintended sign, symptom, syndrome, or illness observed by the investigator or reported by the participant during the study), percentage of participants with AE, time to 3-month sustained disability progression (disability progression was defined as an increase from baseline in EDSS score of at least 1-point or at least 0.5-point for participants with baseline EDSS score >5.5), time to 6-month sustained disability progression, number of new or newly enlarging T2 hyperintense lesions, number of gadolinium-enhancing T1-weighted lesions, percent change in brain volume, change in MSFC score, change in SDMT score, chance in FSS score, change in EQ-5D score, and change in MSIS score.

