### 2.9 Data analysis

As for the continuous variable, normality test was performed for all index awaiting assessment. If it is in accordance with normal distribution, it will be described as mean with 95% confidence interval (CI) or with standard deviation (SD), and one-way analysis of variance (ANOVA) was used for comparison in 3 or more groups, independent sample *t*-test was used for comparison in 2 groups, and Pearson correlation was used for correlation analysis between index. If not, it will be described as median with range or interquartile range (IQR), and Kruskal–Wallis one-way ANOVA was used for comparison among 3 or more groups, Mann-Whitney *U* test was used for comparison between 2 groups, and Spearman correlation was used for correlation analysis between index. Regarding categorical variable, it will be presented as frequencies or proportions, and tested by Fisher exact test. Kaplan-Meier method consists of calculating the probabilities of non-occurrence of event at any observed time of event. The Cox proportional-hazards regression model will be used to investigate the association between the survival time or time of event of patients and one or more predictor variables. Subjects with incomplete data will also be included in the analysis. For each variable, the number of subjects with missing data will be documented. Defining the multidimensional characteristics of DDC patients receiving TCM treatment, the types and detailed information of TCM in DDC treatment, as well as possible combinations of TCM treatments and Western medications are significant objectives of DATE-TCM. Based on these objectives, we did not impose any restriction on patients receiving TCM intervenes or western medications or both at different centers, and the relevant information was recorded systematically for further relevant descriptive studies. Notably, determining the long-term safety and efficacy of TCM interventions in the DDC population and the interaction of TCM treatments with DMTs are important goals for the establishment of DATE-TCM as well. The related studies could be performed based on the established registry data with subsequently systematic cases screening and identification criteria for different study purposes (e.g., the efficacy of a specific TCM preparation or a specific combination of TCM preparation and DMT) in order to obtain a relatively consistent treatment context of patients in a given study. Moreover, propensity score methods will be applied in these comparative studies to control for confounding factors to ensure baseline comparability between groups before evaluating the impact of a treatment on expected clinical end point events. Additionally, we will continue to appropriately adapt the detailed statistical methods according to the characteristics and needs of each DATE-TCM-based study. Values of *p* < 0.05 were considered to indicated statistical significance. All data sets were analyzed using SPSS 21.0 Software or Program R (Version 3.5.1).

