In addition to the systematic documentation of TCM application data in DDC, the DATE-TCM also delivers the following advantages: 1) A distinguishing feature of the Chinese national healthcare system is that TCM and western medicine complement and cooperate with each other to guarantee the overall health of the Chinese people. Correspondingly, the choice between conventional and TCM approaches in DDC treatment is not necessarily either/or in China. Thus, DATE-TCM do not impose additional restrictions on the type of participating centers, which allows our study to include not only Chinese medicine hospitals, but also Western medicine hospitals, as well as a certain number of neurological or specialized rehabilitation hospitals or centers. The above facilitates the inclusion of a larger DDC populations in the database. 2) The evaluation of the severity and significance of specific symptoms and their consequences for disease management often varies between physicians and patients. Subsequently, patients-reported outcomes (PROs) are becoming increasingly important for disease monitoring. Based on these, the DATE-TCM not only includes the clinician-reported medical records such as diagnosis, disability status, relapses, and use of DMT, but also has several PROs modules by application of specific scales involving FIS, EQ-5D, and MSIS to better define fatigue, quality of life, disease burden, and disease impact in DDC populations. 3) Validated blood biomarker assays. DATE-TCM includes not only the collection of data information, but also the collection of peripheral blood samples and the detection of related biomarkers such as NFL (a biomarker of neuronal damage), anti-MOG antibody, and anti-AQP4 antibody (biomarkers for diagnosis, disease activity and treatment responsiveness monitoring). These contribute to an objective and multidimensional monitoring and evaluation of the use of TCM in DDC. 4) A significant number of DDC patients are being or have been treated with TCM in regions and countries other than China. In order to better cover a wider range of TCM users, data collection templates in Japanese and English are being constructed. In addition, primary variables and MDS were determined with reference to MS or DDC Registry studies in multiple regions and counties, which allows our data entries to be relatively consistent with other registry studies and facilitates subsequent collaborative and comparative studies to reveal the general characteristics of TCM in DDC management in different geographical areas and the interaction between TCM and western medicine, especially DMT drugs, and standardize and optimize the overall DDC treatment schemes. 5) DATE-TCM provides a relatively long-term follow-up platform (expected to be at least 5 years) for DDC patients, which helps to interpret the long-term safety and efficacy of TCM in DDC and the long-term impact of TCM on the disease course of DDC patients.

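### The primary relapse rate is defined as a count in an unspecified year, without person-time, and the listed tests take no account of observation time

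*Protocol article*

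**What the plan says.** Section 2.6 gives the definition: "The primary outcome is the Annualized Aggregate Relapse Rate, defined as the number of confirmed relapses within a year". The Abstract gives a time point instead: "The primary outcome is Annualized Aggregate Relapse Rate at 5-year follow-up". Table 2 lists only the name, "Annualized Aggregate Relapse Rate", with no window and no denominator.

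The Abstract sets follow-up "for a total of 5 years"; the Discussion says it is "expected to be at least 5 years". Under section 2.4, "relapse information will be follow-up every 3 months by telephone or face-to-face visits", and Table 1 includes the date of each relapse. Section 2.1 lets patients withdraw whenever they wish.

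For continuous variables, section 2.9 says "normality test was performed for all index awaiting assessment". The result then decides between t-test or ANOVA and Mann-Whitney or Kruskal-Wallis. The section also lists Kaplan-Meier, Cox regression and propensity scores, keeps patients with incomplete data in the analysis, and allows methods to be adapted for each later study. It names no method for counts or rates with unequal observation time.

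**The concern.** An aggregate annualised relapse rate is ordinarily the total number of relapses divided by the total patient-years in which they could have been observed. The name of the outcome points to that quantity, but the definition under the name does not. Read literally, a patient who leaves at month 6 without a relapse contributes the same zero as one who is relapse-free throughout, although far less is known about the first.

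The window matters as well. A rate in year 1, a rate in year 5 and an average over five years are different quantities if relapse activity changes over time, and the text does not choose among them.

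Two things are at stake. One is the level of the only primary outcome. The other is any later comparison of treatment groups built on it, which section 2.9 foresees for particular TCM preparations and combinations with DMTs.

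**Working it through.** The documents state no expected relapse rate, dropout rate or power, so there is no figure of the plan to reproduce for this outcome. All rates below are assumptions.

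**1. Effect of leaving out person-time.** Let *L* be a constant true relapse rate, *d* the annual dropout probability (unrelated to relapse risk), *h* = −ln(1 − *d*), and *T* the nominal window in years. Expected observed time per enrolled patient is (1 − e^(−hT)) / h. Dividing relapses by *N* × *T* instead of observed time gives *L* multiplied by (1 − e^(−hT)) / (hT).

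| Assumed *d* | *h* | Ratio, *T* = 1 | Observed years, *T* = 5 | Ratio, *T* = 5 |
|---|---|---|---|---|
| 5% | 0.0513 | 0.975 | 4.41 | 0.882 |
| 10% | 0.1054 | 0.949 | 3.89 | 0.777 |
| 20% | 0.2231 | 0.896 | 3.01 | 0.603 |

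The one-year count is therefore about 2.5% to 10% low, and the five-year count over nominal time about 12% to 40% low. With *L* = 0.40 and *d* = 10%, the results are 0.40 × 0.949 = 0.38 and 0.40 × 0.777 = 0.31. Relapses over observed patient-years return 0.40 in each case. The one-year and five-year figures belong to two different readings of the text and do not add up.

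**2. Effect of the window.** Assume 0.40 per year in year 1, falling 10% each year. Year 5 is 0.40 × 0.9⁴ = 0.26, and the five-year mean is 0.40 × (1 − 0.9⁵) / (5 × 0.1) = 0.33. The year chosen changes the answer even without dropout.

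**3. Effect on the listed tests.** Simulated comparison: equal true rates of 0.40 per year in both groups, gamma-Poisson counts with dispersion 1, 300 patients per group, nominal level 5%. The ranges cover repeated runs of 1,000 or 2,000 simulations.

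| Follow-up in the two groups | Analysis | False rejection |
|---|---|---|
| 4.5 vs 3.5 years | Mann-Whitney, raw counts | 56–58% |
| 4.5 vs 4.0 years | Mann-Whitney, raw counts | 16–18% |
| Uniform 3–5 vs uniform 0.5–5 years | Mann-Whitney, per-patient rates | 30–33% |
| Uniform 0.5–5 years in both | Mann-Whitney, counts or rates | about 5% |
| Unequal follow-up as above | Negative binomial, log-time offset, dispersion at its true value | 3–6% |

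The error comes from a difference in retention between groups. Over-dispersion and variable follow-up that are the same in both groups leave it near 5%.

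**4. What person-time does not repair.** Take half the patients at 0.6 per year and half at 0.2 (mean 0.40), with 10% annual dropout in the low-rate half and twice that hazard in the high-rate half. The pooled person-time rate is 0.38, against 0.26 for the count over *N* × 5. This is better, but still biased.

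**The case against.** The strongest reply is that the wording is loose rather than wrong. The outcome is called an annualised rate, the phrase about a year can be read as per year, and a per-year rate assessed at five years fits the Abstract. A reader might infer that section 2.6 and the Abstract contradict each other; because of this reading the documents support only an unreconciled window. Even so, the definition as written supplies neither denominator nor window. It is stated text that does not match the name, not detail left to an analysis plan.

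It can also be said that nothing commits the sponsor to dividing by nominal time or comparing raw counts, that section 2.9 never ties the t-test or Mann-Whitney route to relapses, and that every participant receives TCM, so no between-group primary comparison is fixed. This stands as far as it goes: the bias is conditional on literal use, and the false-rejection figures on differential retention. But no listed method accounts for observation time in a recurrent-event rate. Cox regression and Kaplan-Meier address time to an event, and propensity scores address baseline balance. The clause on adapting methods does not correct the definition. The per-patient-rate result shows that the per-year reading alone does not make a rank test safe.

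Two further inferences are not supported. A reader might argue that staggered entry makes follow-up unequal, but follow-up runs from each patient's baseline for five years and no common closing date is stated; withdrawal is the firmer ground. A reader might also extend the point to the adverse event outcomes, such as "Total number of adverse events during evaluation", but a total and a percentage of participants are conventional descriptive summaries, and the percentage has its own denominator.

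**Conclusion.** The point holds as a defect in the stated definition of the only primary outcome: a count without person-time, in a year that is not specified, not reconciled with the Abstract's five-year point, and with no listed test for numeric variables that uses observation time.

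Under an assumed annual dropout of 5% to 20%, unrelated to relapse risk, literal use would understate the rate by about 2.5% to 10% for a one-year count, or about 12% to 40% for a five-year count over nominal time. Rank tests on counts or per-patient rates would mislead if compared groups differed in retention. Both sizes rest on assumptions, since the documents give no dropout, retention or relapse figures. They show what could follow from the text, not that the registry's result will be biased by these amounts.

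**What to change.** In section 2.6, define the primary outcome as total confirmed relapses divided by total patient-years observed, counted from enrolment to year 5 or last contact, whichever comes first, with all patients included whatever their length of follow-up. Put the same definition and window in the Abstract and Table 2.

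In section 2.9, state that this outcome is estimated, and where groups are compared is compared, with a count model for over-dispersed data (for example negative binomial) with log follow-up time as offset and 95% confidence intervals, in place of the normality test followed by t-test or Mann-Whitney.

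The cost is a few sentences and slightly more analysis work. No new data are needed, because relapse dates are already recorded and relapse status is collected every three months. Person-time does not remove bias from dropout that is related to relapse risk, and the text should acknowledge that limit.

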**Primary outcomes**
Annualized Aggregate Relapse Rate
**Secondary outcomes**
Total number of adverse events during evaluation
Percentage of participants with adverse events
Time to 3-month sustained disability progression
Time to 6-month sustained disability progression
Number of new or newly enlarging T2 hyperintense lesions as measured by magnetic resonance imaging (MRI)
Number of gadolinium-enhancing T1-weighted lesions as measured by MRI
Percent change in brain volume as measured by MRI
Change in multiple sclerosis functional composite (MSFC) score
Change in symbol digit modalities Test (SDMT) score
Chance in fatigue severity scale (FSS) score
Change in euroQol- 5 dimension (EQ-5D) score
Change in multiple sclerosis impact scale (MSIS) score

The Secondary outcomes include total number of adverse events (AE, any unfavorable and unintended sign, symptom, syndrome, or illness observed by the investigator or reported by the participant during the study), percentage of participants with AE, time to 3-month sustained disability progression (disability progression was defined as an increase from baseline in EDSS score of at least 1-point or at least 0.5-point for participants with baseline EDSS score >5.5), time to 6-month sustained disability progression, number of new or newly enlarging T2 hyperintense lesions, number of gadolinium-enhancing T1-weighted lesions, percent change in brain volume, change in MSFC score, change in SDMT score, chance in FSS score, change in EQ-5D score, and change in MSIS score.

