## 2 Method and analysis

### 2.1 Study design

DATE-TCM is a prospective, multi-center, observational, disease-based registry of DDC patients treated with TCM in a real-world setting, designed to determine the general characteristics of DDC patients treated with TCM, the types of TCM intervenes, the long-term safety and efficacy of TCM treatment, and the interaction of TCM intervenes and DMTs in the management of DDC. The registry protocol follows the Declaration of Helsinki and Tokyo guidelines for humans and was approved by the Ethics committee of Dongzhimen Hospital, Beijing University of Chinese Medicine (2022DZMEC-171-02) as the coordinating center and will be approved by the local ethics committee of all participant centers. Prior to inclusion in the DATE-TCM, patients or their legally authorized representatives are informed of their conduct by medical staff and must sign a written informed consensus before data collection commences. In this consent form, patients can give permission for relevant biological specimens to be collected and their data to be used for further research activities. Patient participation will be entirely voluntary, with the ability to withdrawal from DATE-TCM participation at any time, and without the need to provide an explanation.

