	DMT current (Generic name, date of start, dose, frequency), TCM type current (TCM preparation, acupuncture, moxibustion, massage, taiji, qigong), detailed use of TCM preparations (name of TCM preparation or information on commercial products, date of start, dose, frequency, composition of TCM preparation including herbal, animal, mineral, and other natural materials, forms of TCM preparation including pills, powders, soft extracts, pellets, decoctions, and medicated liquor), Additional medicine/supplements	○	◎
Safety assessments	AEs, SAEs		◎
CSF	LP date, LP performed at (relapse/remission), Number of Mono and leukocytes, protein content, OCB, IgG index, anti-AQP4 IgG, anti-MOG IgG	○	◎
MRI	MRI date, T2 lesions (total number), New or enlarged T2 lesions (number), Gd-enhanced T1 lesions (total number), Quantitative/volumetric MRI, Brain Parenchymal fraction, Normalized total brain volume, Normalized total lesion volume in white matter	○	•
Other examinations	Evoked potentials (Visual, Somatosensory, Brainstem)	○	◎
	Blood leukocyte count and classification count, Blood liver and renal functions test, Serum NFL, Serum cytokines, Serum anti-AQP4 IgG, Serum anti-MOG IgG	○	☉
Specific scales	BMI, EDSS	○	◎
	MSFC, SDMT, FSS, MSIS, EQ-5D	○	☉
Four examinations of TCM	Inspection, listening and smelling examination, inquiry, palpation	○	◎
Relapse	Relapse date, Affected functional system, severity, Any treatment performed, recovery after relapse		◎

Note: DDC, demyelinating Diseases of the Central Nervous System; MS, multiple sclerosis; SPMS, secondary progressive multiple sclerosis; DMT, disease modifying therapy; TCM, traditional Chinese medicine; CSF, Cerebro-Spinal Fluid; AEs, adverse events; SAEs, severe adverse events; LP, lumbar puncture; OCB, oligoclonal bands; AQP4, Aquaporin-4; MOG, myelin oligodendrocyte glycoprotein; MRI, magnetic resonance imaging; NFL, neurofilament light chain; BMI, body mass index; EDSS, expanded disability status scale; MSFC, multiple sclerosis functional composite; SDMT, symbol digit modalities test; FSS, fatigue severity scale; MSIS, multiple sclerosis impact scale; EQ-5D, EuroQol-5D.

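### The two adverse-event outcomes have no person-time basis or fixed time point, so they are sensitive to unequal follow-up, and SAEs have no separate outcome

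*Protocol article*

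**What the plan says.** Section 2.6 and Table 2 of the protocol article give safety two secondary outcomes: "Total number of adverse events during evaluation" and "Percentage of participants with adverse events". An adverse event is "any unfavorable and unintended sign, symptom, syndrome, or illness observed by the investigator or reported by the participant during the study", with no limit by severity.

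The safety row of Table 1 collects both AEs and SAEs every 3 months. The note to that table reads "SAEs, severe adverse events". No outcome in Table 2 is specific to SAEs.

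On follow-up, the Abstract states that "regular follow-up visits will be implemented every 3–6 months for a total of 5 years", and the Discussion expects at least 5 years. Section 2.1 makes participation voluntary, "with the ability to withdrawal from DATE-TCM participation at any time".

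Section 2.9 presents categorical variables as frequencies or proportions, tested by Fisher's exact test. It keeps subjects with incomplete data in the analysis. It also describes Kaplan-Meier and Cox methods for event times in general, without tying them to adverse events. It names long-term safety of TCM as an important goal and leaves comparative studies to later projects that will use propensity scores and adapted methods.

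**The concern.** A raw count grows in direct proportion to the person-years observed. A crude percentage also rises with observation time, though less than proportionally. When patients leave at different times, both figures mix how often events occur with how long patients were watched. Other outcomes in Table 2 carry time in their definition: the relapse rate is annualised and disability progression is a time to event. The two safety outcomes do not.

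At stake is the reading of the long-term safety result. A TCM type, centre or DMT combination with poorer retention could show fewer events and a lower percentage at an identical event rate. The propensity scores planned for later comparisons balance baseline factors and do not by themselves correct unequal follow-up.

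The second part concerns SAEs. Because every adverse event counts alike, a mild symptom and a serious event weigh the same, and the listed outcomes do not show SAEs apart from the rest.

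**Working it through.** **Inputs from the article.** Planned follow-up is 5 years (Abstract) and enrolment is up to 2000 patients (section 2.3). The article states no AE rate, SAE rate or withdrawal rate, so there is no safety figure to reproduce.

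**Assumptions, for illustration only.** A constant event rate r per person-year; a constant withdrawal hazard w that is independent of events, with w = -ln(1 - yearly withdrawal); N = 2000 for the counts.

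**Formulas.**
- Complete follow-up: percentage with an event = 1 - exp(-5r).
- With withdrawal: crude percentage = r/(r + w) × [1 - exp(-5(r + w))].
- Mean follow-up = [1 - exp(-5w)]/w; expected number of events = N × r × mean follow-up.

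**Worked case, r = 0.1.**
- 5% yearly withdrawal: w = 0.0513, so 0.1/0.1513 × [1 - exp(-0.7565)] = 0.661 × 0.531 = 35.1%.
- 20% yearly withdrawal: w = 0.2231, so 0.1/0.3231 × [1 - exp(-1.6157)] = 0.309 × 0.801 = 24.8%.
- No withdrawal: 1 - exp(-0.5) = 39.3%.

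**Effect of retention at r = 0.1.**

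| Yearly withdrawal | Mean follow-up (years) | Crude % with event | Expected events, N = 2000 |
|---|---|---|---|
| 0% | 5.00 | 39.3 | 1000 |
| 5% | 4.41 | 35.1 | 882 |
| 10% | 3.89 | 31.3 | 777 |
| 20% | 3.01 | 24.8 | 603 |

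In every row the rate per person-year is the same, for example 882/8821 = 0.10 and 603/6026 = 0.10, or 10 per 100 person-years. Under the same assumptions a Kaplan-Meier estimate at 5 years targets 39.3% in every row.

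**Effect of the event rate, 5% versus 20% yearly withdrawal.**

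| r per person-year | Complete 5 years | 5% withdrawal | 20% withdrawal | Ratio |
|---|---|---|---|---|
| 0.02 | 9.5% | 8.4% | 5.8% | 0.69 |
| 0.1 | 39.3% | 35.1% | 24.8% | 0.71 |
| 0.3 | 77.7% | 70.7% | 53.2% | 0.75 |
| 1.0 | 99.3% | 94.6% | 81.6% | 0.86 |

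The true ratio is 1 in every row. A smaller retention gap gives a smaller distortion: 5% versus 10% at r = 0.1 gives 31.3/35.1 = 0.89. With equal retention the ratio is 1.

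**Staggered entry.** If each patient is followed for 5 years, a two-year enrolment period causes no inequality. Only if the data were cut for everyone 5 years after the start, with uniform entry over two years (3 to 5 years of follow-up), would the percentage at r = 0.1 be 32.9% instead of 39.3%. The article states no such cut-off.

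**SAEs.** Setting Table 1 beside Table 2, SAEs are recorded quarterly and fall within the AE definition in section 2.6, so they enter both AE outcomes. What is absent is an outcome that shows them separately.

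**The case against.** The strongest reply is that Table 2 names outcomes, not estimators, and that a condensed article leaves denominators and time points to a full protocol or analysis plan that is not shown. Kaplan-Meier and Cox are planned in general and could cover time to first adverse event. No between-group safety comparison is fixed here, and later comparative studies will choose their own methods. This reply has weight, and it limits the point to what the article does fix. But the article fixes the safety measures as a count and a percentage, gives a default analysis for percentages that ignores exposure, and keeps incomplete subjects in. Followed as written, the result depends on retention.

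A reader might infer more than the article supports:
- *That the safety result mainly reflects length of observation.* No withdrawal rate is given, the distortion vanishes with complete follow-up, and at a fixed 5 years the percentage still runs from 9.5% to 99.3% as the event rate goes from 0.02 to 1.0.
- *That this is an open cohort with follow-up of unplanned length.* A 5-year period is planned.
- *That SAEs enter no outcome.* They count as adverse events.
- *That patients who leave because of harm lower the percentage.* A patient who withdraws after a recorded adverse event still counts in it. Such withdrawal can reduce only the total count, or hide events that were never reported.

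The *severe* wording in the Table 1 note is, fairly, a minor correction that would not merit a point on its own.

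**Conclusion.** The point holds in this form: the two listed safety outcomes lack a person-time denominator and a fixed time point, so they are sensitive to unequal follow-up in a registry with free withdrawal and long-term safety as a goal; and SAEs, though collected every 3 months, have no separate outcome.

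The size is conditional. At an assumed 0.1 events per person-year, 5% versus 20% yearly withdrawal produces 35.1% versus 24.8% with no true difference; across the assumed rates of 0.02 to 1.0 the apparent ratio is 0.69 to 0.86. It moves to 1 as retention becomes equal, and nothing is distorted if all patients complete 5 years. These figures rest on constant rates and on withdrawal unrelated to events, neither of which the article can confirm.

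**What to change.** In Table 2 and section 2.9:
- Report AEs and SAEs per 100 person-years of follow-up with 95% CI.
- Report the cumulative incidence of first AE and of first SAE at stated times, by Kaplan-Meier, which is already planned, or by a competing-risk estimate.
- List SAEs as a separate secondary outcome.
- Keep the crude total and percentage as description.
- Correct the Table 1 note from *severe* to *serious* adverse events.

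Report by time on TCM or DMT only where stop dates or duration are recorded. Table 1 lists start and end dates for previous medication, but only a start date for current DMTs and TCM preparations; section 2.5 mentions duration for CHM.

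The overall rates need no new data, since AEs and SAEs are already collected every 3 months. The cost is slightly more analysis work and one clarification to sites on SAE coding. Person-time and Kaplan-Meier estimates correct for unequal follow-up but not for withdrawal that is itself related to event risk.
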